### Study summary

**Figure 1** provides an overview of the study flow. Participants will be randomly allocated to either the ECT or MST group. Each center aims to recruit 15 participants for each group (ECT and MST), using block randomization, resulting in a total of 30 participants per center (15 per group). Across seven centers, this will yield a total sample size of 210 participants (105 per group). The trial comprises a 12-session intervention phase of ECT/MST, spanning approximately 4 weeks, followed by a 12-week observation period. For the first three treatment sessions, participants will receive consecutive sessions. Subsequently, there will be a one-day interval between sessions 4 to 6, a two-day interval between sessions 7 to 9, and a three-day interval between sessions 10 to 12, ensuring completion within a month. Following treatment completion, participants will undergo follow-up clinical observations every four weeks for 12 weeks. EEG and ECG recordings will be obtained at baseline, post-session 3, 6, 9, 12 (3 hours after each session), and at the 12-week follow-up. All evaluations will be conducted under standardized conditions throughout the sessions. **Table 1** delineates the time points for clinical assessments, interventions, and electrophysiological examinations.

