#### Secondary outcomes

The secondary outcomes include: changes in HAMA, SDS, SAS, and GAF scores over time; changes in the seven secondary cognitive variables (TMT-A, BACS SC, Category Fluency Test, CPT-IP, WMS-III SS, BVMT-R, NAB Mazes); and changes in rsEEG and ECG HRV variables.

Relapse is defined as an HDRS-24 total score of 16 or higher, with at least a 10-point increase from the lowest post-treatment score, sustained across two visits at least 1 week apart. If rescue treatment (e.g., maintenance ECT, adjusted pharmacotherapy) is administered before Week 12, outcomes will be recorded up to the point of intervention to assess time-to-relapse.

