MST will be conducted at 100 Hz and 100% output using a pulse width of 350 μs and a peak intensity of the magnetic field at 3.0 Tesla. The duration of magnetic stimulation will be titrated using a 10-second train duration, starting from 2 seconds and increasing by 4 seconds in subsequent sessions, up to a maximum of 10 seconds (i.e., 200–1,000 pulses per session). In cases of poor seizure quality (<15 s), the stimulation duration increment will be set to 6 seconds in the next session. If no seizures were elicited, an additional 10-second stimulation will be administered immediately. Subsequent MST treatments will be maintained at a 10-second duration for a total of 1000 pulses.

EEG recordings during MST and ECT will be obtained using the Thymatron IV device with left and right frontal leads.

Patients will undergo identical preparation procedures, including the placement of earplugs and skin preparation for ECT electrode placement, irrespective of treatment allocation. To maintain blinding, the auditory stimulus from a recorded MST session will be played during ECT administration to prevent treatment allocation disclosure to individuals in adjacent rooms.

Completers will be defined as patients who received at least 8 treatments or achieved remission before the eighth treatment. Relapse will be defined as an HDRS-24 total score of 16 or higher, with at least a 10-point increase in HDRS-24 score sustained across two visits at least 1 week apart, the emergence of psychotic or suicidal symptoms, or the need for readmission to inpatient care.

While 12 sessions are standard for acute-phase treatment, the potential need for more sessions in MST will be explored through *post-hoc* analyses. This trial’s design prioritizes comparability with ECT’s typical acute regimen while allowing for long-term outcome assessment to capture delayed benefits.

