### Additional treatments

As the primary objective of this trial is to evaluate efficacy, participants are restricted from receiving concurrent treatments for their depressive symptoms, except for one type of antidepressant medication, during the 30-day intervention period. However, the use of psychoactive medications and psychotherapy is allowed during the 12-week follow-up period, with detailed documentation of the type, dosage, and frequency/session of medication or psychotherapy.

During the 12-week follow-up period, participants may receive maintenance ECT, pharmacotherapy (e.g., antidepressants, mood stabilizers), or psychotherapy to prevent relapse. The type, dosage, and frequency of maintenance treatments will be recorded in detail to assess their impact on outcomes.

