Appropriate statistical methods will be employed for data analysis, including mixed-effects models for repeated measures (MMRM). MMRM with a factorial design (3 time points × 2 conditions) will be conducted to examine significant interactions between time (baseline, Day 30, and Week 12) and condition (ECT and MST), while adjusting for potential covariates such as age, sex, duration of illness, age of onset, IQ, and antidepressant usage. This approach is robust to missing data under the missing-at-random (MAR) assumption and provides unbiased estimates of treatment effects. The significance level will be set at 0.05.

Sensitivity analyses will be performed to assess the robustness of results to missing data, including multiple imputation (MI) under MAR and missing-not-at-random (MNAR) assumptions. Results from MMRM and MI will be compared. Exploratory analyses will include subgroup analyses by demographic/clinical characteristics and correlation analyses between neurophysiological biomarkers (EEG/ECG) and treatment outcomes, using linear or logistic regression models as appropriate.

Subgroup analyses will compare relapse rates and time-to-relapse between participants who received maintenance treatments versus those who did not, within both MST and ECT groups. This will help disentangle the effects of acute treatment from post-treatment management strategies.

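### The received/not-received maintenance comparison of relapse is confounded by indication and open to immortal-time bias, so it cannot separate acute from post-treatment effects; the relapse event is also defined in two unreconciled ways.

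*Protocol article*

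**What the plan says.** All references are to the protocol article.

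- **Data entry and analyses.** Subgroup analyses within both the MST and ECT groups will "compare relapse rates and time-to-relapse between participants who received maintenance treatments versus those who did not". The stated purpose is: "This will help disentangle the effects of acute treatment from post-treatment management strategies".
- **Additional treatments.** During follow-up, "participants may receive maintenance ECT, pharmacotherapy (e.g., antidepressants, mood stabilizers), or psychotherapy to prevent relapse". Type, dosage and frequency are to be recorded. Nothing in the section randomises maintenance or fixes when it starts.
- **Secondary outcomes.** "Relapse is defined as an HDRS-24 total score of 16 or higher, with at least a 10-point increase from the lowest post-treatment score", sustained over two visits at least a week apart. The same section continues: "If rescue treatment (e.g., maintenance ECT, adjusted pharmacotherapy) is administered before Week 12", outcomes are recorded only up to that intervention, for the time-to-relapse assessment.
- **ECT and MST procedures.** A second relapse definition keeps the score of 16 and the 10-point rise but does not say from what point the rise is measured. It adds "the emergence of psychotic or suicidal symptoms, or the need for readmission to inpatient care".
- **Study summary and Table 1.** After treatment, "participants will undergo follow-up clinical observations every four weeks for 12 weeks", that is, at Weeks 4, 8 and 12.

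**The concern.** Maintenance status is known only after randomisation, and it is decided by clinicians and patients who can see how the patient is doing. Two biases follow.

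- **Indication.** Patients judged likely to relapse are more likely to be given maintenance, so the treated group carries more underlying risk.
- **Immortal time.** If maintenance begins in, say, Week 6 and counts only when it precedes relapse, that patient had to be relapse-free for six weeks to enter the treated group. Anyone who relapsed earlier falls into the untreated group.

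The first bias makes maintenance look harmful and the second makes it look protective. Neither is addressed by the covariates listed for the mixed model (age, sex, duration of illness, age of onset, IQ, antidepressant usage).

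Two further problems sit in the event itself. Maintenance ECT and pharmacotherapy appear both as the grouping variable and as rescue that ends recording. And whether a readmitted patient without a sustained score rise has relapsed depends on which section is followed. At stake is a published statement about maintenance that could be an artefact in either direction.

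**Working it through.** The plan gives no relapse rate, maintenance share or start times, so there is no figure of its own to reproduce here. Everything numerical below is an assumption, chosen to show the mechanism.

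**Inputs.** 12-week relapse risk p = 30% (assumed), constant hazard, no maintenance effect. Half the patients are planned for maintenance, with the start uniform over weeks 0 to a, for a = 4 or a = 12 (assumed). Follow-up is 12 weeks (Study summary).

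Hazard: λ = −ln(0.70)/12 = 0.02972 per week. The probability that a planned patient is still relapse-free at the start is q = (1 − e^(−λa))/(λa).

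**Rule 1: only starts before relapse count as received.**
- Relapse among received: (q − 0.70)/q.
- Relapse among not received: [0.5 × 0.30 + 0.5 × (1 − q)] / [0.5 + 0.5 × (1 − q)].
- a = 4: q = 0.9428. Received 0.2428/0.9428 = 25.8%. Not received 0.1786/0.5286 = 33.8%.
- a = 12: q = 0.8411. Received 0.1411/0.8411 = 16.8%. Not received 0.2295/0.5795 = 39.6%.

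**Rule 2: starts in Weeks 0-4, and half of the relapsers not yet treated are treated afterwards and counted as received.**
- Half of 0.1786 is 0.0893 of the cohort, which moves across.
- Received: (0.1214 + 0.0893)/(0.4714 + 0.0893) = 37.6%.
- Not received: 0.0893/(0.5286 − 0.0893) = 20.3%.

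The sign reverses although maintenance does nothing in either case.

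**Range under Rule 1.** The same formulas with p = 20% give 17.0% vs 22.8% (a = 4) and 10.7% vs 27.5% (a = 12). With p = 50% they give 44.0% vs 54.8% and 30.7% vs 60.9%. A separate simulation used exponential start times, 20-50% relapse and 30-70% starting maintenance. Its spurious rate ratios were 0.32 to 0.45.

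**Stopping at the start of treatment.** If follow-up also ends when maintenance starts, as the rescue sentence reads literally, the received group under Rule 1 has 0% relapse by construction. The other group had 23-67% in that simulation.

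**Adding indication.** A shared risk factor was put on both the relapse and the maintenance hazards, with half starting maintenance:

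| SD on log-hazard | Received/not-received ratio | Time-varying exposure | Week-4 landmark |
|---|---|---|---|
| 0 (range above) | 0.32-0.45 | 0.99-1.01 | 0.99-1.02 |
| 0.5 | 0.51-0.52 | 1.23-1.27 | 1.28-1.31 |
| 1.0 | 0.77-0.91 | 1.73-2.06 | 1.96-2.30 |

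Handling time correctly removes the immortal-time part. It leaves confounding by indication, which needs adjustment.

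**The two definitions.**

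| | Secondary outcomes | ECT and MST procedures |
|---|---|---|
| Score | ≥16 | ≥16 |
| Rise | ≥10 from lowest post-treatment score | ≥10, reference not stated |
| Two visits ≥1 week apart | yes | yes |
| Psychotic or suicidal symptoms | no | yes |
| Readmission | no | yes |

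**Confirmation.** The score rule in Secondary outcomes asks for a rise "with at least a 10-point increase from the lowest post-treatment score, sustained across two visits at least 1 week apart". A crossing first seen at Week 12 has no later scheduled visit. Under the 30% constant hazard, the share of relapses beginning in Weeks 8-12 is (0.70^(8/12) − 0.70)/0.30 = (0.7884 − 0.70)/0.30 = 29%.

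**The case against.** The strongest reply is that this is a subsidiary analysis. It follows the exploratory analyses, relapse is not in the article's list of secondary outcomes, and the stated purpose is only that the comparison will help. That stands: it limits the reach of the point but does not make the comparison valid for its stated purpose.

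Second, the article never defines *received* or says when maintenance starts. An antidepressant continued from the treatment phase would leave little immortal time. In the simulation without shared risk, counting any start in the 12 weeks, including after relapse, gave a ratio of 0.99-1.01. This also stands. A reader might infer that the relapse result is bound to be an artefact of known direction; the documents do not support that. They support only that size and sign hang on an unstated rule, and that indication remains under any rule.

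Third, the smaller gap is within noise. In a full arm of 105 under Rule 1 with a = 4, the groups are about 50 and 55 and the standard error is √(0.258×0.742/49.5 + 0.338×0.662/55.5) = 8.9 points, against a gap of 8. For a = 12 (about 44 and 61) it is 8.4 points against 23. So the bias may or may not show up in one arm.

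Three other readings go too far:
- That the analysis applies both relapse definitions. It names neither; the fault is that two sections are unreconciled.
- That a Week-12 crossing can never be confirmed. This holds on the scheduled visits only, since nothing excludes an unscheduled one.
- That no MST-versus-ECT relapse comparison is planned. The full plan, not shown here, may contain one.

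**Conclusion.** The point holds in this limited form. As written, the comparison rests on a non-randomised, post-randomisation grouping. It is confounded by indication and, for any maintenance begun during follow-up, exposed to immortal-time bias, so it cannot carry the separating claim attached to it. The structural fault does not depend on any assumed figure. The sizes do: about 26% vs 34%, 17% vs 40%, or 38% vs 20% with zero true effect, under 30% relapse, half planned for maintenance, and different start windows and grouping rules. These figures include no indication bias, which pulls against the immortal-time bias and leaves the net result uninterpretable.

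Separately, the document contradicts itself on what counts as relapse. It also treats maintenance ECT and pharmacotherapy as permitted prevention in one section and as rescue that ends recording in another. The primary HDRS-24 comparison and the sample size are not affected. This should be corrected, but it does not threaten the trial's main conclusion.

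**What to change.** 1. Reconcile Secondary outcomes with ECT and MST procedures so that there is one relapse definition, including the reference point for the 10-point rise. Which definition is adopted is for the investigators.
2. Reconcile the rescue sentence in Secondary outcomes with Additional treatments, and keep recording relapse after maintenance or rescue starts. Without those events, a time-varying analysis has nothing to work with.
3. Make the comparison of randomised arms the main relapse analysis.
4. Replace the received/not-received split with maintenance as a time-varying exposure from its recorded start date, or with a Week-4 landmark. Adjust for HDRS-24 severity before maintenance.
5. Label that result descriptive and delete the claim that it separates acute from post-treatment effects.
6. Count unconfirmed Week-12 crossings as relapses in a sensitivity analysis.

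Most of this is analysis wording. The article already calls for detailed maintenance records; the start date must be among the items captured. Item 2 is the only one that changes data collection. Its cost should be small, because the Week 4, 8 and 12 visits are already scheduled.

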## Discussion

Our study design features several strengths. Firstly, we have enrolled a sizable sample size and meticulously documented participants’ electrophysiological characteristics throughout the entire ECT/MST treatment process and the subsequent follow-up period. This comprehensive approach adds significant value to our study by providing a detailed understanding of the effects of these therapies. Secondly, we have implemented a strict blindng protocol, a challenging aspect in ECT and MST studies. To ensure the quality of blinding, third-party evaluators have been invited for assessment. Moreover, patients undergo identical preparation for both ECT and MST treatments, and the MST device emits similar sounds during sessions to maintain blinding. Thirdly, we have made efforts to control confounding factors by allowing only a single stable dose of antidepressant medication during the treatment process. Fourthly, while previous comparisons between ECT and MST often view MST as a mere replacement for ECT, our study aims to optimize treatment decisions through personalized electrophysiological signals. Lastly, there is currently a lack of efficacy prediction models based on EEG and ECG physiology in seizure therapy (41, 42). If our study can establish an effective model, it will provide a novel tool for guiding precision seizure therapy.

However, our protocol is not devoid of risks and potential limitations, which we strive to address. Firstly, depression is a chronic and fluctuating condition, and the 12 sessions of stimulation and 12-week follow-up planned for our patients may not be adequate to induce or fully capture significant improvements. While a more intensive regimen with increased cumulative sessions over time and longer follow-up duration would be beneficial, it is currently beyond the scope of our protocol due to constraints on time and resources. Secondly, individuals with MDD, despite sharing similar depressive symptoms, may be influenced differently by various biological factors such as inflammation, genetic susceptibility, or aberrant brain function, which can impact the effectiveness of ECT/MST treatment. Although our methods incorporate objective measures of EEG and ECG physiology, they only represent a fraction of the etiology of MDD and cannot encompass all biological subtypes of MDD. Lastly, the neurobiological mechanisms underlying the effects of ECT/MST on MDD remain largely unclear. While our study includes the collection of EEG and ECG signals to investigate the electrophysiological mechanisms of seizure therapy, these assessments are conducted offline and can only provide limited insights into the mechanisms of action. Future studies could consider additional assessments, such as brain functional characteristics based on magnetic resonance imaging (43, 44), to further elucidate the neural mechanisms of seizure therapy on brain function.

One notable limitation is the use of an age-based dosing method for ECT (80% of the patient’s age in years × 100 mC), which is less precise than seizure threshold titration. This approach may lead to suboptimal dosing in some patients, such as underdosing in younger individuals with higher seizure thresholds or overdosing in older adults with lower thresholds, potentially increasing the risk of cognitive side effects or reducing treatment efficacy. The decision to use age-based dosing reflects common clinical practice in many Chinese centers, where titration protocols are not yet universally adopted due to resource constraints or training variability. While this aligns with real-world settings, it introduces variability in ECT dosing that could affect the comparability of safety and efficacy outcomes with MST. Future studies using more personalized dosing strategies (e.g., titration) are needed to validate the generalizability of our findings. An additional limitation is the absence of a dedicated autobiographical memory test in our cognitive assessment battery. Autobiographical memory is a domain frequently reported to be sensitive to ECT-mediated cognitive impairments, and its exclusion may limit our ability to fully capture differences in this specific memory function between MST and ECT. Future studies are encouraged to incorporate validated autobiographical memory measures to complement assessments of verbal learning and memory and provide a more comprehensive evaluation of cognitive effects.
